### Data collection and management

This study will systematically collect baseline data (demographics, medical history, abdominal symptoms assessments [using the Gastrointestinal Symptom Rating Scale (45), GSRS], intervention parameters (electrostimulation settings, acupoint localization, compliance), efficacy endpoints, and safety profiles. Data will be recorded via electronic date capture and paper-based case report forms (CRFs) during screening, intervention, and follow-up phases, with real-time entry and logic verification. Two individuals will independently enter and verify the data for error correction, and participant information will be anonymized. The Ethics Committee will conduct random audits for quality control to ensure the authenticity and traceability of the data.

### Statistical analysis

All statistical analyses were performed using SPSS 29.0 and GraphPad Prism 10.4, adhering to the intention-to-treat (ITT) principle. Continuous variables were tested for normality using the Shapiro–Wilk test; normally distributed data were expressed as mean ± standard deviation, and non-normally distributed data as median [interquartile range]. Categorical variables were presented as frequencies and percentages. For the primary outcome (rate of adequate bowel preparation), a multivariable logistic regression model was employed to adjust for baseline covariates. Missing data were handled using Multiple Imputation by Chained Equations (MICE); 20 imputed datasets were generated, and the imputation model included all baseline variables, the grouping variable, and the primary outcome measure. To control the type I error rate for multiple secondary outcomes, a hierarchical strategy was adopted. The primary outcome was tested at *α* = 0.05. Among secondary outcomes, colonoscopy indicators were designated as key secondary endpoints and were corrected using the Holm-Bonferroni method. For these endpoints, insertion and withdrawal times (continuous variables) were compared using independent *t*-tests or Mann–Whitney *U* tests as appropriate, and cecal intubation and adenoma detection rates (categorical variables) were compared using Chi-square or Fisher’s exact tests. The remaining secondary outcomes, including bowel movement parameters, patient satisfaction scores, and adverse reactions, were treated as exploratory analyses; no multiplicity correction was applied, and *p*-values are presented for descriptive reference only. Safety profiles were described by comparing the incidence and severity of adverse events (Chi-square test) and patient satisfaction (Wilcoxon rank-sum test). Protocol deviations were addressed by per-protocol sensitivity analyses to verify the robustness of the results. A two-sided *p* < 0.05 was considered statistically significant.

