### Sample size

The sample size was calculated using a two-sample proportion test, with the following parameters: a two-sided significance level (*α*) of 0.05, a statistical power of 90% (*β* = 0.1), an expected qualified preparation rate of 70% for the sham TEAS group, and 85% for the active TEAS group. The calculated minimum evaluable sample size was 161 per group. Accounting for a 20% dropout rate, a total of 404 subjects were planned, with 202 subjects allocated to each group.

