### Outcomes

#### Primary outcome

The primary outcome measure was the rate of adequate bowel preparation, which was assessed by two gastroenterologists through independent review of endoscopic videos using the Boston Bowel Preparation Scale (BBPS) (33). The BBPS was applied to each of the three segments of the colon (right, including cecum and ascending colon; transverse, including hepatic and splenic flexures; and left, including descending colon, sigmoid and rectum). Each colon region received a “segment score” ranging from 0 to 3, and these scores were summed to calculate a total BBPS score (0–9) (refer to Appendix). Adequate bowel preparation was defined as a total BBPS score ≥6 with each colon segment scoring ≥2 after standard washing and air insufflation for luminal distension during colonoscopy (13, 44). Endoscopists maintained blinding to group allocation throughout the trial. All endoscopic imaging was independently evaluated by two gastroenterologists, with final diagnoses established through consensus deliberation and unresolved discrepancies resolved by a third-party senior specialist.

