### Adverse reaction

Adverse reaction associated with bowel preparation and colonoscopy procedures—including nausea, vomiting, abdominal pain, bloating, headache, and dizziness—were prospectively categorized by blinded independent assessors.

1) Transient symptoms requiring no intervention, with preserved procedure tolerability;
2) Symptom-driven procedural pauses (<5 min) without compromising examination completion;
3) Intolerable symptoms necessitating premature procedure termination;

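### All missing primary outcomes are imputed as missing at random, with no separate rule for examinations lost because preparation failed

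*Protocol article*

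**What the plan says.** The Primary outcome section has two gastroenterologists score the BBPS from endoscopic video in three colon segments: "Adequate bowel preparation was defined as a total BBPS score ≥6 with each colon segment scoring ≥2". In the Appendix, a segment hidden by solid stool that cannot be cleared scores 0.

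The Statistical analysis section follows the intention-to-treat principle and handles missing data by MICE with 20 datasets. On content, "the imputation model included all baseline variables, the grouping variable, and the primary outcome measure". No exception is made for the reason an outcome is missing. The one sensitivity analysis named is directed at deviations: "Protocol deviations were addressed by per-protocol sensitivity analyses to verify the robustness of the results".

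The Sample size section expects "an expected qualified preparation rate of 70% for the sham TEAS group, and 85% for the active TEAS group" and allows for 20% dropout. The Secondary outcomes section collects first defecation time, defecation frequency and final stool consistency. The Appendix grades adverse reactions, the third grade being "Intolerable symptoms necessitating premature procedure termination".

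**The concern.** The endpoint exists only if there is video of the colon. A patient whose examination is cancelled because the preparation was not finished, or abandoned because of stool before all segments are seen, may have no complete score. For that patient the reason for missingness is closely tied to the outcome itself.

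Imputation from baseline variables and arm assumes that, given those variables, missing patients resemble the examined ones. It therefore fills in a preparation failure at about the success rate of patients who were examined. The trial's hypothesis is that TEAS improves preparation and eases its symptoms, so the frequency of such events could plausibly differ by arm. If they are commoner in sham, a real benefit is diluted. If they are commoner under TEAS, an apparent benefit can arise where there is none. The per-protocol analysis would not show either, because it does not vary the missing-at-random assumption.

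**Working it through.** **The plan's own figure.** Inputs from the Sample size section: 70% against 85%, "a two-sided significance level (*α*) of 0.05", power 90%. With pooled variance and no continuity correction, the mean rate is 0.775 and

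n = [1.960·√(2·0.775·0.225) + 1.282·√(0.70·0.30 + 0.85·0.15)]² / 0.15² = 161 per arm.

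This matches: "The calculated minimum evaluable sample size was 161 per group". Then 161/0.80 = 201.25, rounded up to 202 per arm and 404 in total. The sample size is correct and is not at issue.

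**What the imputation does.** At 20% missing, 0.20 × 202 ≈ 40 patients per arm have no outcome. Filled at the arm's own rate, about 0.70 × 40.4 = 28 sham patients and 0.85 × 40.4 = 34 TEAS patients become adequate. That is reasonable for unrelated losses and wrong for preparation failures.

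**Size of the error, with 70% and 85% as the true rates in all randomised patients.** Let a proportion m of an arm be preparation failures with no score. The rate among scored patients is p/(1 − m), and imputation from arm reproduces it approximately. Unrelated random missingness leaves this rate unchanged. The m values are assumptions.

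| True rates | m sham / m TEAS | Rates after imputation | Difference | True difference |
|---|---|---|---|---|
| 70 / 85 | 6% / 2% | 0.70/0.94 = 74.5%; 0.85/0.98 = 86.7% | 12.3 | 15 |
| 70 / 85 | 4% / 4% | 0.70/0.96 = 72.9%; 0.85/0.96 = 88.5% | 15.6 | 15 |
| 70 / 70 | 3% / 8% | 0.70/0.97 = 72.2%; 0.70/0.92 = 76.1% | +3.9 | 0 |
| 70 / 70 | 3% / 5% | 72.2%; 0.70/0.95 = 73.7% | +1.5 | 0 |
| 70 / 70 | equal | equal | 0 | 0 |

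Simulation (3,000 trials per scenario, 202 per arm, 4% unrelated missingness, 20 arm-specific imputations, Rubin's rules, Wald test) agrees. In the 6%/2% case power is about 85%, against about 95% when the failures are counted as failures. In the null 3%/8% case type I error is about 14 to 15%, against about 5%.

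The primary model is logistic, so the odds ratio matters too. The true value is (0.85/0.15)/(0.70/0.30) = 2.43. At 4%/4% it becomes (0.85/0.11)/(0.70/0.26) = 2.87, so an error that is small in percentage points is less small on this scale. Under no effect with equal rates it stays at 1.

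**Alternative reading: 70% and 85% as rates among scored patients.** Imputation then always shows about 15 points. If all missing patients are preparation failures and are counted as such:

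- 10%/10%: 0.90 × 70 = 63.0% and 0.90 × 85 = 76.5%, a difference of 13.5 (imputation 1.5 too high).
- 5%/10%: 66.5% and 76.5%, a difference of 10.0 (5.0 too high).
- 10%/5%: 63.0% and 80.75%, a difference of 17.75 (2.75 too low).

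If only a quarter of the missing patients are failures and missingness is equal at 5 to 20%, the error is +0.2 to +0.8 points. If none are, it is zero.

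**The case against.** Four objections carry weight.

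- A reader might infer that patients already seen to be badly prepared are imputed as adequate. The documents do not support that. A dirty segment that is examined scores 0 or 1, and one segment below 2 settles the outcome as inadequate. No text sets such a record to missing. The point is confined to examinations that never took place or stopped before the outcome was determined.
- A reader might also treat every third-grade adverse reaction as a known failure. That grade concerns symptoms such as nausea, pain and dizziness, not stool, and the colon may be clean. These cases may be left to imputation unless a segment below 2 was seen.
- The larger errors need unequal event rates. Sham uses the same device and settings, patients are supervised inpatients, and cecal intubation is to be at least 95%. That target is a benchmark, not a guarantee, and may not count cancelled procedures. Taking 5% as a ceiling, the null 3%/5% case gives only 1.5 points. The 20% dropout figure covers all causes.
- Imputation from baseline, arm and outcome is a standard approach, and a condensed article may leave auxiliary variables and sensitivity analyses to a fuller plan.

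These narrow the point but do not remove it. The article states the method and the model's contents and makes no exception by reason, so the rule as written does not fit the subset whose outcome is missing because preparation failed.

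**Conclusion.** The point holds in a conditional form. As written, the imputation treats examinations lost to failed preparation like any other loss and would fill them in at roughly 70 to 85% adequate. The resulting bias is possible rather than certain, and it can take either sign. Under assumed event rates it is about −2.7 points (12.3 instead of 15) at 6% sham/2% TEAS and about +3.9 points under no effect at 3%/8%. At equal rates of 4% it is about +0.6 points, and under no effect with equal rates it is zero. These figures assume that every such patient is a true failure and that imputation approximates the arm's observed rate. The documents give no rate for these events. A claim that the planned analysis is biased as it stands would go further than they allow. This should be fixed, with importance depending on how many such cases occur and how they divide between arms.

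**What to change.** 1. State that a patient with any observed segment score below 2, or whose examination was cancelled or incomplete because of inadequate preparation, counts as inadequate without imputation. Add a case report form field for the reason a BBPS is missing or incomplete, completed blind to allocation.
2. Impute only the remaining missing outcomes, including examinations ended for symptoms with no segment below 2. Add final stool consistency, defecation frequency and adverse-reaction grade, all already collected, as auxiliary variables.
3. Add a delta-adjusted (tipping-point) analysis of the imputed outcomes. Keep the per-protocol analysis for deviations, since it does not test missing at random.

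The cost is a few sentences of analysis wording, one form field and a little more analysis work. Observed adequate rates will be slightly lower in both arms. The rule should be fixed before unblinding. If a fuller plan already contains it, the article needs only a sentence saying so.

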#### Secondary outcomes

Defecation parameters

Following TEAS/sham-TEAS interventions, patients documented their defecation parameters in the record sheets, including first defecation time, total defecation frequency, and final stool consistency.

Colonoscope outcomes

The evaluated parameters encompassed four key indicators: insertion time, withdrawal time, cecal intubation rate (CIR), and adenoma detection rate (ADR). The insertion phase was defined as commencing with initial rectal visualization and concluding when the endoscope tip traversed the ileocecal valve into the cecal caput. Withdrawal time represents the duration from cecum to anal canal during meticulous mucosal inspection in screening or diagnostic procedures without therapeutic interventions, with a minimum 6-min benchmark indicating thorough pathological evaluation. CIR, which reflects procedural completeness through comprehensive cecal visualization including anatomical landmarks, must be maintained at ≥95% to ensure examination adequacy. ADR calculated as the percentage of colonoscopies with at least one adenoma identified.

Adverse reaction

Research staff documented all adverse reactions occurring during the bowel preparation process and post-colonoscopy, including nausea, vomiting, abdominal pain, distension, headache, and dizziness (refer to Appendix). The incidence rate of adverse reactions was calculated as (number of cases with adverse reactions)/(total number of cases).

Satisfaction and follow-up colonoscopy

At the conclusion of the treatment period, all participants were surveyed regarding their satisfaction with bowel preparation and their willingness to have a follow-up colonoscopy. The details are presented in Appendix.

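### The stated imputation model leaves out post-randomisation data the trial already collects and, as listed, does not cover the Holm-tested colonoscopy endpoints, although ITT is claimed for every analysis

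*Protocol article*

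**What the plan says.** All references are to the protocol article.

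- **Analysis principle** (Statistical analysis): "All statistical analyses were performed using SPSS 29.0 and GraphPad Prism 10.4, adhering to the intention-to-treat (ITT) principle".
- **Missing data** (same section): "Missing data were handled using Multiple Imputation by Chained Equations (MICE); 20 imputed datasets were generated", followed directly by the model's contents: "the imputation model included all baseline variables, the grouping variable, and the primary outcome measure".
- **Key secondary endpoints** (same section): "colonoscopy indicators were designated as key secondary endpoints and were corrected using the Holm-Bonferroni method". The two times are compared by t-test or Mann–Whitney test, while "cecal intubation and adenoma detection rates (categorical variables) were compared using Chi-square" or Fisher's exact test. Neither imputation nor pooling is mentioned for these comparisons.
- **Denominator for adenoma detection** (Secondary outcomes): "ADR calculated as the percentage of colonoscopies with at least one adenoma identified".
- **Data recorded after randomisation**: in Secondary outcomes, "patients documented their defecation parameters in the record sheets, including first defecation time, total defecation frequency, and final stool consistency". Data collection and management adds compliance with the intervention. The Appendix grades adverse reactions, the top grade being symptoms that end the procedure early.
- **Expected loss** (Sample size): "Accounting for a 20% dropout rate, a total of 404 subjects were planned".

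**The concern.** Multiple imputation is only as good as the variables that make missing-at-random plausible. Here the primary outcome can be missing because the colonoscopy did not take place, was stopped, or left no usable video. How the preparation went may influence all of these. The trial records how it went, through the defecation diary, compliance and adverse-reaction grade, but the listed model uses none of it. A missing BBPS result is therefore drawn from baseline data and arm alone.

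The second issue is scope. A variable outside a chained-equations model is not imputed. The four colonoscopy endpoints that carry the Holm-corrected tests are not listed, yet ITT is claimed for all analyses. Reading the list as predictors only, with the secondary endpoints imputed from it, helps little. When no colonoscopy is done, BBPS and the four indicators are missing together, so the primary outcome adds no information about them.

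At stake are some bias in the primary risk difference if missingness follows the course of the preparation, and a confirmatory family whose analysis population is not the one claimed.

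**Working it through.** **1. The plan's own figures.** Inputs from Sample size: 70% v 85%, two-sided α = 0.05, power 90%, 20% dropout. With pooled variance under the null and p̄ = 0.775:

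n = [1.960·√(2·0.775·0.225) + 1.2816·√(0.70·0.30 + 0.85·0.15)]² / 0.15² = [1.157 + 0.745]² / 0.0225 ≈ 160.8, so 161 per group.

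161/0.8 = 201.25, so 202 per group and 404 in total. Both figures reproduce. The allowance is 0.20 × 404 ≈ 81 patients.

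**2. Closed-form illustration.** None of these inputs is in the documents. Assume clear final stool in 60% (sham) v 90% (TEAS), and adequate preparation in 90% if clear and 40% if not.

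- Sham: 0.6·0.9 + 0.4·0.4 = 0.70. TEAS: 0.9·0.9 + 0.1·0.4 = 0.85. These match the planning rates.
- Let BBPS be missing in 10% if stool is clear and 35% if not. The expected observed rates are:
  - Sham: (0.54·0.9 + 0.26·0.4)/0.80 = 0.590/0.800 = 73.75%.
  - TEAS: (0.81·0.9 + 0.065·0.4)/0.875 = 0.755/0.875 = 86.3%.

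A model that knows only the arm reproduces these observed rates:

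| Missing if clear / not clear | Arms affected | Sham | TEAS | Difference (true 15) |
|---|---|---|---|---|
| 10% / 20% | both | 71.4% | 85.5% | 14.1 |
| 10% / 35% | both | 73.75% | 86.3% | 12.5 |
| 5% / 45% | both | 76.1% | 87.0% | 10.9 |
| 10% / 35% | TEAS only | 70.0% | 86.3% | 16.3 |

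The last row shows that the bias is not always towards zero.

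**3. Simulation with other assumptions.** There were 202 per arm, true rates 70% v 85%, and 3,000 runs. A binary stool indicator is always observed, with the sensitivity/specificity for adequate preparation shown. Stool-dependent missingness is 12% if clear and 40% if not. Across the indicators, that is 18% per arm (0.12·0.795 + 0.40·0.205 = 0.177) to 25% (0.12·0.54 + 0.40·0.46 = 0.249). In the sham-only column, the TEAS arm loses 20% at random. Stratifying on stool within arm stands in for imputation with the auxiliary. Cells give the estimated difference in points, without / with the stool variable.

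| Sens./spec. | Unrelated to stool (20%) | Related, both arms | Related, sham only |
|---|---|---|---|
| 0.60/0.60 | 14.85 / 14.84 | 14.17 / 14.78 | 13.34 / 14.89 |
| 0.75/0.75 | 14.90 / 14.88 | 13.37 / 14.93 | 11.13 / 14.90 |
| 0.90/0.80 | 14.94 / 14.94 | 12.94 / 15.08 | 9.84 / 15.06 |

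Power with missingness unrelated to stool: 89.2% v 89.3%, 90.4% v 91.4%, 89.5% v 91.8%. The gain is 0.1 to 2.3 points. With missingness related to stool, the bias without the variable runs from 15 − 14.17 = 0.8 to 15 − 9.84 = 5.2 points. For the weakest indicator with both arms affected, power does not improve (86.4% v 86.1%); only the bias falls.

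**4. A key secondary endpoint on observed cases.** Use the step 2 assumptions with 10%/35% missing, and mean insertion time of 6 min if clear and 9 min if not. The true difference is 3·(0.90 − 0.60) = 0.90 min. Among observed patients the clear shares are 0.81/0.875 = 0.926 and 0.54/0.80 = 0.675, so the difference is 3·0.251 = 0.752 min, or 84% of the true value.

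**The case against.** The strongest reply is that this is a condensed article whose SAP is not shown, that the listed model follows directly on the primary regression, and that it is a valid model under missing at random given its variables. Much of this stands. Leaving out an auxiliary variable is a weakness, not an error, and separate models for secondary endpoints may exist. What remains is that the article does not merely stay silent: it states the model's contents and claims ITT for all analyses.

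A reader might infer several stronger things that the documents do not support:

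- **That the key secondary tests are complete-case by plan.** The article never says so; it follows only if the list is taken as exhaustive.
- **That the planned tests rule out pooling.** Chi-square, Fisher and Mann–Whitney p-values do not feed Rubin's rules directly. But the t-test rests on a mean difference and standard error, and a 2×2 table gives a risk difference with a variance; both can be pooled.
- **That counting adenoma detection per colonoscopy is a missing-data failure.** It is the protocol's own definition.
- **That every absent time should be imputed.** Withdrawal time is defined only for procedures without therapy, and insertion time has no end point if the cecum is not reached. Such values are undefined, not missing.
- **That stool result is known to predict BBPS, or is always available.** Neither is stated, and patients who leave early may have no final stool entry.

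The illustrations also use arm alone in place of a model with all baseline data. To the extent that baseline data explain the link between missingness and cleansing, the losses are overstated.

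**Conclusion.** The point holds as a worthwhile improvement to a stated method, not as an error that invalidates the primary analysis. The listed model omits collected post-randomisation data that would make missing-at-random more credible. As listed, it also provides no imputation for the Holm-tested endpoints to which the ITT claim extends.

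The size is conditional. If missingness is unrelated to how the preparation went, nothing is biased and at most about 2 points of power are at stake. If it is related, the risk difference moves by about 1 to 5 points in the scenarios tried. It shrinks when both arms or only the sham arm are affected, and grows by about 1 point when only the TEAS arm is. This rests on stool predicting BBPS, being observed when BBPS is missing, and baseline data adding no prediction. The sample size is unaffected.

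**What to change.** **Primary outcome.** Extend the imputation sentence so that the model also contains, as auxiliary variables, time to first defecation, number of defecations, final stool consistency, compliance, adverse-reaction grade and, where observed, the procedure indicators. The last help when only the video is lost. Auxiliaries belong in the imputation model only, not among the covariates of the primary logistic regression.

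**Key secondary endpoints.** Choose one and state it:

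1. Drop the ITT claim for these endpoints and label them as analyses of colonoscopies performed. This fits the present definition of adenoma detection.
2. Keep the ITT claim. Define which values are missing and which are undefined, and impute only the former: not withdrawal time in therapeutic procedures, nor insertion time when the cecum is not reached. Pool a mean difference or risk difference by Rubin's rules, apply Holm to the pooled p-values, and keep the planned tests on observed data as sensitivity analyses. Adenoma detection would then need a definition per randomised patient.

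Under option 2, cecal intubation needs care. At the protocol's 95% benchmark there are at most about 0.05 × 202 ≈ 10 failures per arm, so a rich logistic imputation model could be unstable.

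**Cost.** A change of wording and a somewhat larger imputation model to check. All the variables are already collected, no patients or visits are added, and N stays at 404.

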Acupuncture is a nonpharmaceutical technique that originated in China and has been used for over 3,000 years. TEAS is a modification of traditional acupuncture (58–60), which combines the advantages of acupuncture and percutaneous electrical nerve stimulation. Unlike traditional acupuncture requiring skin penetration, this transcutaneous approach exhibits notable application prospects via its non-invasive nature, user-friendly operation, and portability (27, 61–63), while concurrently reducing infection risks and improving patient compliance (64). In recent years, a growing number of investigations have put a spotlight on the therapeutic effects of TEAS in intestinal dysmotility disorders. Clinical trials demonstrated that ST36 acupoint stimulation effectively enhances spontaneous bowel movements, alleviates constipation symptoms, and improves quality of life (65), while PC6 application demonstrates marked efficacy in reducing postoperative nausea and vomiting incidence within 24 h (66). While transabdominal or abdominal surface stimulation is theoretically more direct, limb acupoint TEAS is a superior adjunctive choice based on current evidence and operational feasibility. This study implemented a standardized stimulation parameter protocol (0.5-ms pulse width, 25 Hz frequency, and 2–10 mA amplitude) (42, 43, 67), developed based on prior clinical trial evidence to ensure intervention stability and experimental reproducibility. This study recruited only inpatients, which may limit the generalizability of our findings to the broader outpatient colonoscopy population. The inpatient setting was chosen to ensure protocol adherence and intervention fidelity, but future multicenter, pragmatic trials in outpatient settings are needed to validate the real-world applicability of TEAS as an adjunct to bowel preparation. Additionally, although we standardized endoscopist experience and withdrawal time, ADR remains influenced by multiple operator-dependent factors, and residual confounding cannot be fully excluded.

This protocol employs validated stimulation parameters (25 Hz frequency, 60-min sessions) combined with standardized laxative regimens, aiming to establish TEAS as a safe strategy for enhacing bowel preparation and alleviating adverse effects (e.g., bloating and nausea).

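### The key secondary endpoints are tested without covariate adjustment and the test for the two time endpoints is left open; this is valid but gives up precision, most clearly for adenoma detection

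*Protocol article*

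**What the plan says.** The Statistical analysis section uses multivariable logistic regression with baseline covariates for the primary outcome. The four colonoscopy indicators (insertion time, withdrawal time, cecal intubation rate and ADR) are key secondary endpoints under Holm–Bonferroni. For the two rates the section states that "cecal intubation and adenoma detection rates (categorical variables) were compared using Chi-square" or Fisher's exact test. The two times are compared by independent t-test or Mann–Whitney U test, whichever is judged suitable. None of the four has a covariate or endoscopist term.

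The same section states: "Continuous variables were tested for normality using the Shapiro–Wilk test". It ties that result to the choice of summary statistics (mean with SD, or median with interquartile range).

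The Discussion says that endoscopist experience and withdrawal time were standardised, but that "ADR remains influenced by multiple operator-dependent factors, and residual confounding cannot be fully excluded". The Colonoscopy section refers to senior endoscopists in the plural and gives no number. The Randomization and blinding section describes concealed 1:1 block randomisation and names no endoscopist stratum. The Data collection and management section lists demographics, medical history and a baseline symptom score; it does not list endoscopist identity.

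**The concern.** The article names operator influence as a source of variation in ADR, describes no stratification for it, and then fixes an ADR test that cannot account for it. It also adjusts the primary outcome but none of the endpoints next in line, although demographic and medical-history data will be in hand for every patient. Variation that those data could explain stays in the error term. This matters more here because the trial was sized for the primary outcome alone and the first Holm step of four uses alpha 0.05/4 = 0.0125.

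A second, smaller issue concerns the two times. A t-test compares means and a Mann–Whitney test compares rank distributions. If the choice waits for the shape of the trial data, the hypothesis tested for two of the four multiplicity-controlled endpoints is not fixed in advance.

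At stake is the chance of detecting a real effect on these endpoints, and the clarity of what is being tested. The false-positive rate of the two-sample tests is not at stake.

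**Working it through.** **1. The plan's own figure.** The Sample size section gives "a two-sided significance level (*α*) of 0.05", 90% power, "an expected qualified preparation rate of 70% for the sham TEAS group, and 85% for the active TEAS group". With pooled variance and no continuity correction:

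n = [1.960·√(2·0.775·0.225) + 1.282·√(0.70·0.30 + 0.85·0.15)]² / 0.15² = 160.8, so 161 per group.

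This matches "The calculated minimum evaluable sample size was 161 per group". Dividing by 0.80 gives 161/0.80 = 201.25, so 202 per group, which matches "Accounting for a 20% dropout rate, a total of 404 subjects were planned, with 202 subjects allocated to each group". The primary sample size is sound and this point does not touch it. The article states no power for the key secondary endpoints.

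**2. Insertion and withdrawal times.** Inputs: 202 per arm (Sample size section, the most favourable case) and alpha 0.0125 (first Holm step). Assumed: a standardised effect d that has 80% unadjusted power at two-sided 0.05, and a share R² of outcome variance explained by covariates.

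- d = (1.960 + 0.842)·√(2/202) = 0.279
- Power = Φ(d·√(n/2)/√(1−R²) − z), with n = 202, d·√(n/2) = 2.802, and z = 1.960 (alpha 0.05) or 2.498 (alpha 0.0125)

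| R² (assumed) | Equivalent sample size, 1/(1−R²) | Power, alpha 0.05 | Power, alpha 0.0125 |
|---|---|---|---|
| 0 (unadjusted) | 1.00 | 80.0% | 61.9% |
| 0.05 | 1.05 | 82.0% | 64.7% |
| 0.10 | 1.11 | 84.0% | 67.6% |
| 0.20 | 1.25 | 87.9% | 73.7% |
| 0.30 | 1.43 | 91.8% | 80.3% |

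The alpha of 0.0125 applies only to the smallest of the four p-values. Later Holm steps use 0.0167, 0.025 and 0.05, so the two power columns bracket the procedure.

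**3. ADR.** Simulation of 404 patients randomised 1:1, 3,000 runs per setting, two-sided alpha 0.05. Chi-square was compared with logistic regression containing endoscopist indicators. Assumed: six endoscopists, a log odds ratio of 0.6, a base ADR of 25% or 35%, and a between-endoscopist SD on the logit scale as shown.

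| Base ADR | Endoscopist SD | Unadjusted power | Adjusted power | Gain (points) |
|---|---|---|---|---|
| 25% | 0.3 | 76.5% | 76.4% | −0.1 |
| 25% | 0.5 | 74.9% | 77.6% | 2.7 |
| 25% | 0.8 | 67.6% | 72.5% | 4.9 |
| 35% | 0.3 | 81.5% | 82.9% | 1.4 |
| 35% | 0.5 | 79.7% | 82.5% | 2.8 |
| 35% | 0.8 | 72.6% | 79.0% | 6.4 |

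With one prognostic covariate added to the data and to the adjusted model (base 25%, endoscopist SD 0.5), power rises from 71.2% to 75.1% for a covariate effect of 0.5 logits per SD, and from 66.2% to 72.9% for 0.8. The gains are 3.9 and 6.7 points.

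**4. Validity.** With no treatment effect, the unadjusted ADR test rejected in 4.6% to 5.5% of runs across all settings. The adjusted test rejected in 4.5% to 6.0%. The Monte Carlo standard error is √(0.05·0.95/3000) = 0.4 points, so the unadjusted test shows no inflation.

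**5. Cecal intubation.** The Secondary outcomes section requires a rate of at least 95%. If that is met, there are at most about 0.05 × 404 = 20 failures in the whole trial, too few for a model with several covariates.

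**The case against.** The strongest reply is that simple two-sample tests for secondary endpoints of a randomised trial are conventional, valid and clearly named, and that supplementary adjusted analyses may sit in an analysis plan not shown here. The Discussion sentence on ADR is then an honest limitation and contradicts nothing. The size of any gain depends on inputs the article does not give, and for ADR it is nil if endoscopists differ little. All of that stands, and it limits this point to efficiency and prespecification. It does not remove it, because the article names the tests for these endpoints and so makes a choice.

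Three stronger readings are tempting but unsupported:

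- A reader might infer that the unadjusted comparison is biased by endoscopist imbalance. Allocation is concealed and randomised, and endoscopists are blinded to it. Imbalance is then chance variation, which the two-sample test already allows for. The groups do occupy separate wards during stimulation, but nothing in the article links a ward to particular endoscopists.
- A reader might infer that the plan calls all four key secondary endpoints operator-dependent. It says so of ADR only.
- A reader might infer that the Shapiro–Wilk result formally selects the test for the times. The article ties it to the descriptive summaries. That it also guides the test is a natural reading but is not stated. What is stated is that the choice between the two tests is open, and that is enough for the prespecification point.

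**Conclusion.** The point holds as a weakness in efficiency, consistency and prespecification. The named tests are valid, and neither the primary analysis nor the sample size is affected.

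For the times at the first Holm step, the illustrative gain is about 3 to 18 points of power (61.9% to between 64.7% and 80.3%), on an assumed d of 0.279, 202 analysable patients per arm and an assumed R² of 0.05 to 0.30. Fewer analysable patients would lower every power figure, but the equivalent sample-size ratio 1/(1−R²) would not change. For ADR at alpha 0.05, the gain is about 0 to 6 points from endoscopist alone and about 4 to 7 with a prognostic covariate, on assumed base rates, number of endoscopists and spread between them. For cecal intubation little is to be gained. The case is clearest for ADR because there the article supplies the reason to adjust.

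**What to change.** Before unblinding, prespecify for the key secondary endpoints:

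- **Insertion and withdrawal time:** linear regression of log time, reported as a ratio of geometric means.
- **ADR:** logistic regression, reported as a standardised risk difference so that the effect stays on the same marginal scale as the simple comparison of proportions.
- **Covariates in these models:** arm, age, sex, the baseline covariates of the primary model (to be listed), and endoscopist if identity is recorded. The Data collection and management section does not list it, so confirm this or add it to the case report form. State in advance how endoscopists with few cases will be pooled.
- **Cecal intubation:** Fisher's exact test, fixed in advance because few failures are expected.
- **Test selection:** remove the open choice between t-test and Mann–Whitney. Report the unadjusted tests as sensitivity analyses, naming one for each endpoint.

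The Holm–Bonferroni procedure can stay as it is, applied to the p-values from these analyses. The cost is a change of wording, a little more analysis work, the pooling rule and possibly one added data field. No further patients or procedures are needed.
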